## 7.2. Specifications of Study Population Analyses

### 7.2.1. Subject Disposition

Based on all screened subjects, the number and percentage of randomized subjects and those who discontinued prior to randomization along with the reasons will be summarized.

Based on all enrolled subjects, the number and percentage of subjects will be summarized:

- Subjects who received cerebral angiography
- Subjects who did not receive cerebral angiography and reasons
- Subjects who completed the study
- Subjects who discontinued from the study prematurely and primary reasons
- Subjects included in each analysis set.

### 7.2.2. Demographic and Baseline Characteristics

Demographics and baseline characteristics will be summarized for the FAS.

- Age (years), sex, race, baseline body weight and height will be collected from the “Demography” Page of Case Report Form (CRF).
- mRS score will be collected from the “Modified Rankin Scale (mRS)” Page of CRF.
- Smoking history and alcohol history will be collected from the “Smoking and Alcohol History” Page of CRF.
- BMI (kg/m^2) calculated as  $[\text{weight}(\text{kg})/(\text{height}(\text{cm})/100)^2]$  and rounded to keep one decimal place.

### 7.2.3. Prior Medical History

- Prior medical history will be collected from the “Prior Medical History” Page of CRF.
- Prior medical history will be summarized for the FAS as per **Table 3**.
- All prior medical history data will be listed by subject.

### 7.2.4. Current Admission Diagnosis

- Current admission diagnosis will be collected from the “Cocurrent Medical History” Page of CRF.
- Current admission diagnosis will be coded using the latest version of Medical Dictionary for Regulatory Activities (MedDRA). All diagnoses will be listed, and the number and

percentage of subjects with each diagnosis will be summarized alphabetically by system organ class (SOC) and decreasing frequency by preferred term (PT).

### 7.2.5. Pre-Operation Imaging Examination

- Artery diameter measurements will be collected from the “Pre-Operation Imaging Examination” Page of CRF
- Radial artery growth status will be collected from the “Radial Artery Growth Evaluation” Page of CRF

### 7.2.6. Concomitant Medications

- Concomitant medications will be collected from the “Concomitant Medication” Page of CRF.
- All medications will be coded and summarized using the latest version of WHO-DD, presenting the number and percentage of subjects by the Anatomical Therapeutic Chemical (ATC) classification system and the preferred name (PN); each subject could have medications under multiple ATC Level 3 groups and/or multiple preferred drug names, but each subject will be counted only once within each ATC Level 3 group and preferred name class. In case that any drug has not been assigned a Level 3 ATC group, the group with the most specific level will be used.

## 8. Efficacy Analyses

### 8.1. Primary Efficacy Endpoint(s) Analyses

#### 8.1.1. Overview of Planned Primary Efficacy Endpoint(s) Analyses

The primary endpoint(s) analyses will be based on the FAS population, unless otherwise specified.

Table 4 provides an overview of the planned primary endpoint analyses.

**Table 4 Overview of Planned Primary Endpoint(s) Analyses**

|                                                           | Data Displays Generated |        |         |
|-----------------------------------------------------------|-------------------------|--------|---------|
|                                                           | Table                   | Figure | Listing |
| Rate of Successful Diagnostic Cerebral Angiography |                         |        |         |
| Descriptive statistics:
Number of subjects with:       |                         |        |         |
| – Successful diagnostic cerebral angiography              | Y                       |        | Y       |
| – Failed diagnostic cerebral angiography                  |                         |        |         |
| ○ With crossover                                          |                         |        |         |
| ○ Without crossover                                       |                         |        |         |

|                                                                                                | Data Displays Generated |        |         |
|------------------------------------------------------------------------------------------------|-------------------------|--------|---------|
|                                                                                                | Table                   | Figure | Listing |
|                                                                                                |                         |        |         |
| Number of subjects with failed diagnostic cerebral angiography per stage and causes of failure |                         |        |         |
| Success rate and failure rate of diagnosis with 95% confidence intervals (CI)                  |                         |        |         |
| Difference in rates of successful diagnosis between TRA and TFA groups and its 95% CI          |                         |        |         |
| P value for non-inferiority test                                                               |                         |        |         |
| Risk Ratio (RR) between TRA and TFA groups and its 95% CI                                      |                         |        |         |

## 8.1.2. Specifications of Primary Efficacy Endpoint(s) Analyses

### 8.1.2.1. Definitions and Derivations

The primary effectiveness endpoint of this study is the rate of successful diagnostic cerebral angiography, which is defined as the aortic arch vessel is successfully superselected without changing the puncture site, with angiography results meeting the diagnostic requirements. Any change of puncture site before or during the procedure after a subject has been randomized would be treated as a diagnosis failure.

### 8.1.2.2. Analysis Methods

#### 8.1.2.2.1. Overview of Analysis Methods

| Analysis                | Analysis Set | Statistical Analysis Methods                                                                                                                                                                 | Handling of Missing Data                             |
|-------------------------|--------------|----------------------------------------------------------------------------------------------------------------------------------------------------------------------------------------------|------------------------------------------------------|
| Primary Endpoint |              |                                                                                                                                                                                              |                                                      |
| Primary analysis        | FAS          | Normal approximation method for calculating 95% CI of rates;
Normal approximation method for calculating 95% CI of difference in rates;
Wald Z test;
Generalized linear regression. | Missing primary outcome will not be included in FAS. |
| Supplementary analysis  | PPS          | Same as primary analysis.                                                                                                                                                                    | Missing primary outcome will not be included in PPS. |

#### 8.1.2.2.2. Analysis Methods of Primary Analysis

- The success rate and failure rate of diagnosis will be described, and the causes of failure will be summarized.
- The Wald method will be used to calculate the 95% confidence intervals (CI) for rate of successful diagnosis in TRA and TFA groups
- The difference in rates between TRA and TFA groups will be presented with its 95% CI according to Wald method.
- A Wald Z test will be used for the non-inferiority hypothesis of the primary efficacy endpoint with a non-inferiority margin of -5%.
- A generalized linear regression with log link function will also be used to calculate risk ratio (RR) between the two groups and its 95% CI. The covariates only include study group. Association between baseline factors and the success rate of diagnostic cerebral angiography will be explored in exploratory analysis section.

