### **7.3 Sample Size Estimation**

This study will test the hypothesis that the success rate of diagnostic cerebral angiography by TRA approach is not inferior to that by TFA approach.

We assume the success rates of diagnostic cerebral angiography by TRA and TFA are 97% and 98% respectively by considering the data in the references, with a margin for non-inferiority of -5%, a power of 90% at one-side significance level of 0.025, and a drop-out rate of 10%, 429 cases are needed for each group according to PASS 15 software, and thus a total of 858 subjects need to be enrolled in this study.

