### **7.7.1 Primary Effectiveness Analysis**

The primary effectiveness endpoint of this study is the success rate of diagnostic cerebral angiography, which is defined as the aortic arch vessel is successfully selected without changing the puncture site, with angiography results meeting the diagnostic requirements. Any change of puncture site before or during the procedure after a subject has been randomized would be treated as a diagnosis failure.

The success rate and failure rate of diagnosis will be described, and the causes of failure will be summarized (see Section 2.2 Study Endpoints for details). The Clopper-Pearson method will be used to calculate the 95% confidence intervals (CI) for rate of successful diagnosis in both groups, as well as the difference in rates between the two groups and its 95% CI (Miettinen-Nurminen method). Chi-square tests will be used for non-inferiority tests for rates of successful diagnosis in both groups, and Logistic regression will be used to calculate odds ratio (OR) between the two groups and its 95% CI.

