| 
 
The success rate and failure rate of diagnosis will be described, and the causes of failure will be summarized (see Section 2.2 Study Endpoints for details). The Clopper-Pearson method will be used to calculate the 95% confidence intervals (CI) for rate of successful diagnosis in both groups, as well as the difference in rates between the two groups and its 95% CI (Miettinen-Nurminen method). Chi-square tests will be used for non-inferiority tests for rates of successful diagnosis in both groups, and Logistic regression will be used to calculate odds ratio (OR) between the two groups and its 95% CI.
 
 | 
 
The Wald method will be used to calculate the 95% confidence intervals (CI) for rate of successful diagnosis in TRA and TFA groups
 
The difference in rates between TRA and TFA groups will be presented with its 95% CI according to Wald method.
 
A Wald Z test will be used for the non-inferiority hypothesis of the primary efficacy endpoint with a non-inferiority margin of -5%.
 
A generalized linear regression with log link function will also be used to calculate risk ratio (RR) between the two groups and its 95% CI.
 
 | 
 
To keep the consistency between 95% confidence interval and non-inferiority test, the method for calculating confidence intervals for success rates and rate differences was changed to Wald method. And the statistical test was updated from Chi-square test to Wald Z test
 
Since this is a prospective randomized controlled study, we used risk ratio(RR) instead of odds ratio(OR) for between-group comparison
 
 |

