## 3. Sample Size Considerations

This study will test the hypothesis that the success rate of diagnostic cerebral angiography by TRA approach is not inferior to that by TFA approach.

The success rates of diagnostic cerebral angiography by TRA and TFA are assumed to be 97% and 98% respectively. With a margin for non-inferiority of -5% and a drop-out rate of 10%, 429 cases are needed for each group to achieve a power of 90% at one-sided significance level of

0.025, according to PASS 15 software, and thus a total of 858 subjects need to be enrolled in this study.

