## 4. Planned Analyses

### 4.1. Interim Analyses

An independent data and safety monitoring board (DSMB) will be established to regularly review and analyze all safety data and/or efficacy data for the evaluation of potential risks and benefits. Other responsibilities and details of the DSMB will be included in the DSMB Charter.

An interim analysis will be conducted by the DSMB after the 30-day follow-up of 430 participants. The Haybittle-Peto method will be used to control the overall Type I error rate: the p-value boundary for the one-sided test at the interim analysis will be set at 0.001, and the p-value boundary for the one-sided test at the final analysis will be set at 0.024.

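### The SAP's switch to a Wald test and Wald intervals at success rates near 98% pushes the non-inferiority error rate above 0.025, and the stated sample size and power do not describe that test

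*Combined protocol and SAP*

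**What the plan says.** Protocol 7.2 tests a margin of 5 percentage points with a chi-square test at one-sided 0.025. Protocol 7.7.1 adds Clopper-Pearson intervals for each arm and "the difference in rates between the two groups and its 95% CI (Miettinen-Nurminen method").

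SAP 1.1, Table 1, declares the change: "the method for calculating confidence intervals for success rates and rate differences was changed to Wald method", and the test becomes a Wald Z test. The only reason given is agreement between interval and test. SAP 2 keeps the one-sided 0.025 level. SAP 8.1.2.2.2 makes it the primary analysis: "A Wald Z test will be used for the non-inferiority hypothesis of the primary efficacy endpoint with a non-inferiority margin of -5" (per cent). The sample code in SAP 8.1.2.3.1 asks for Wald limits and applies no continuity correction. No score-based sensitivity analysis is planned.

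SAP 3 repeats the protocol's size after the change of test: "429 cases are needed for each group to achieve a power of 90" (per cent). SAP 4.1 adds an interim look at 430 participants, where "the p-value boundary for the one-sided test at the interim analysis will be set at 0.001", with 0.024 at the final analysis.

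**The concern.** The unpooled Wald statistic estimates its variance from the observed rates. Near 100% success, a chance shortage of failures in the TRA arm both improves the observed difference and shrinks the standard error. The statistic then overshoots in the direction of non-inferiority. A score test avoids this by computing the variance at rates constrained to differ by exactly the margin.

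The sole confirmatory claim would therefore be tested at a looser level than the one stated, through a change made after the protocol and in the direction that favours the claim. The stated power would also describe a test other than the one to be run.

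**Working it through.** **Inputs.** Protocol 7.3: "We assume the success rates of diagnostic cerebral angiography by TRA and TFA are 97% and 98% respectively", "with a margin for non-inferiority of -5" (per cent), "a power of 90% at one-side significance level of 0.025", and 10% drop-out. SAP 4.1: interim at 430 participants (about 215 per group), boundaries 0.001 and 0.024.

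**1. The plan's sample size.** 429 × 0.9 = 386 evaluable per group. The uncorrected Wald formula gives

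n = (1.960 + 1.282)² × (0.97 × 0.03 + 0.98 × 0.02) / 0.04² = 319.8, so 320 evaluable; 320 / 0.9 = 356 enrolled.

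The smallest n with 90% exact Wald power is 333 (stable from 340), or 370 to 378 enrolled. Neither is 429. Candidates nearer to it are:

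- continuity-corrected pooled z test, exact power: 386 evaluable, 429 enrolled (exact match);
- Farrington-Manning, exact power: 394, giving 438;
- Gart-Nam, exact power: 378, giving 420;
- asymptotic Farrington-Manning: 408, giving 454.

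**2. Type I error, single look at nominal 0.025.** Both binomials were fully enumerated at the null boundary (TFA rate p, TRA rate p − 0.05), summing the probability of every table that the test rejects.

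| TFA rate | Wald, n=386 | Score, n=386 | Wald, n=429 | Score, n=429 |
|---|---|---|---|---|
| 95% | 0.0281 | 0.0242 | 0.0277 | 0.0239 |
| 97% | 0.0303 | 0.0227 | 0.0296 | 0.0237 |
| 98% | 0.0318 | 0.0219 | 0.0324 | 0.0226 |
| 99% | 0.0366 | 0.0214 | 0.0392 | 0.0209 |
| 99.5% | 0.0430 | 0.0211 | 0.0429 | 0.0213 |

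At 98% the excess is 0.0318 / 0.025 = 1.27 to 0.0324 / 0.025 = 1.30 times nominal. At the 0.024 boundary the Wald error is still 0.0317 (n=386) or 0.0319 (n=429), because the possible tables are discrete.

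**3. With the interim look.** Assume the Wald test is used at both looks. The interim error at 215 per group and nominal 0.001 is 0.0032 at TFA 98%, 0.0060 at 99% and 0.0086 at 99.5%. Simulated overall error of the 0.001/0.024 rule is about 0.030 at 97%, 0.033 at 98%, 0.037 to 0.039 at 99% and 0.042 to 0.047 at 99.5%. The score version gives 0.022 at 98% and 0.018 to 0.019 at 99.5%.

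**4. A result on which the methods disagree.** Take 19/429 failures on TRA and 8/429 on TFA, a difference of −2.56 points.

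- Wald SE = √[(0.9557 × 0.0443 + 0.9814 × 0.0186) / 429] = 0.01189. z = (−0.02564 + 0.05) / 0.01189 = 2.05, p = 0.020; lower 95% limit −4.89%. Non-inferior, even at 0.024.
- Score SE, at rates constrained to differ by 5 points, = 0.01312. z = 0.02436 / 0.01312 = 1.86, p = 0.032. Not shown.

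If TRA is truly 95% or 96% against TFA 98%, about 7% of trials (n=429, boundary 0.024) pass Wald and fail the score test. The reverse has negligible probability.

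**5. Exact power at 97% versus 98%, nominal 0.025.** Wald 93.0% (n=386) and 95.5% (n=429); score 89.2% and 92.2%. At 0.024 the score test gives 88.9% and 92.1%.

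**6. Single-arm 95% Wald intervals.** Coverage at 98% is 94.5% (n=386) or 92.4% (n=429). At 99% and n=386 it is 89.3%. Clopper-Pearson covers 96.2% to 97.8% in these cases. In an illustrative subgroup of 50 per arm at 98%, Wald coverage is about 64%: 0.98⁵⁰ = 36% of samples have no failures and yield a zero-width interval.

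**The case against.** Wald is a recognised large-sample method, the change is disclosed with a reason, and the excess at the planning rate is only 0.7 to 0.8 of a percentage point. At the planned 97% and 98%, Wald and score decisions differ in only about 3% to 4% of trials.

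Several qualifications stand:

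- The PASS procedure is not named, so the test behind 429 is inferred. The one exact match is a continuity-corrected pooled z test, with score tests nearby.
- The protocol's named test was chi-square. Miettinen-Nurminen was its interval for the difference, and Clopper-Pearson applied only to single-arm rates, so dropping the latter does not affect the test's error.
- SAP 4.1 does not name the interim test and defers details to the DSMB charter. The interim and two-stage figures assume Wald.
- A TFA rate of 99.5% and subgroups of 50 per arm are illustrations. Neither is a planning value.
- The trial is not underpowered under Wald.

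None of this restores the stated level. The Wald error exceeds 0.025 at every TFA rate examined, using only the single final test. The reason in Table 1 does not require Wald either, because a Miettinen-Nurminen interval and its matching score test also agree with each other.

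**Conclusion.** The concern holds and should be fixed before analysis. At the plan's own TFA rate of 98%, the primary test runs at about 0.032 instead of 0.025, some 27% to 30% above the stated level. If Wald is also used at the interim, the two-stage error is about 0.033. The excess depends on the true TFA rate, which is unknown: with 386 per group it runs from 0.028 at 95% to 0.037 at 99%, and it grows beyond that. The score test stays at or below 0.0242 across the rates examined.

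The 429 per group and 90% power do not come from the uncorrected Wald test, which needs 356 enrolled by formula. Part of Wald's higher power of 93.0% to 95.5% is bought by the inflated error. These figures assume independent binomial outcomes, equal arms and 386 to 429 evaluable per group.

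**What to change.** - **SAP 2, 8.1.2.2 and 8.1.2.3.1:** make the Farrington-Manning score test primary, with the Miettinen-Nurminen interval for the difference. In SAS, use RISKDIFF with NONINF, METHOD=FM and MARGIN=.05 for the test, and CL=MN(CORRECT=NO) for the interval. Without that correction the interval agrees exactly with the test, which meets the aim stated in Table 1. Keep Wald at most as a sensitivity analysis.
- **SAP 4.1:** name the same score test for the interim and final looks. Reconcile the 0.025 in SAP 2 with the 0.024 final boundary. A test at 0.024 corresponds to a 1 − 2 × 0.024 = 95.2% interval, so a 95% interval will not match it exactly under any method.
- **Single-arm and subgroup rates:** restore Clopper-Pearson, or use Wilson. Apply the same choices to the accurate-diagnosis endpoint, which SAP 8.2.2.2 analyses like the primary.
- **SAP 3:** name the PASS procedure behind 429. State that 429 per group gives about 89% (386 evaluable) to 92% (429 evaluable) power for the score test.
- **SAP Table 1:** update the entry and its rationale.

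The cost is SAP text and a few lines of code. Power returns to about the planned 90%, with no extra patients or data.

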#### 8.1.2.2.3. Analysis Methods of Supplementary Analysis

The analysis will be repeated in PPS using the same methods as primary analysis.

#### 8.1.2.3. Model Specifications

##### 8.1.2.3.1. Model Specifications of Primary Analysis

| Statistical Analysis of Binary Variables                                                                                                                                                                                                                        |
|-----------------------------------------------------------------------------------------------------------------------------------------------------------------------------------------------------------------------------------------------------------------|
| Endpoints and Parameters                                                                                                                                                                                                                                        |
| 
 
• Endpoints: success rate
 
• Parameters: 
 
– Rate estimate and 95% CI
 
– Rate difference and 95% CI
 
– P value
 
– Risk Ratio
 
 
 
 |
| Input Variables                                                                                                                                                                                                                                                 |

- AVAL: Response variable
- TRTPN: Planned arm
- COUNT: The number of subjects in each level each group

### Sample SAS code

#### Rate estimate and 95% CI calculation sample code:

```
PROC FREQ DATA= adeff;
    TABLE AVAL / BINOMIAL (CL=WALD) ALPHA=0.05;
    WEIGHT COUNT/zeros;
    BY TRTPN;
    ODS OUTPUT BINOMIALCLS=BinomialCL;
RUN;
```

#### Rate difference and 95% CI calculation sample code:

```
PROC FREQ DATA=adeff;
    TABLE TRTPN*AVAL / RISKDIFF(CL=WALD) ALPHA=0.05;
    WEIGHT COUNT/zeros;
    ODS OUTPUT PDIFFCLS = diff;
RUN;
```

#### Wald test for non-inferiority sample code:

```
PROC FREQ DATA=adeff;
    TABLE TRTPN*AVAL / RISKDIFF(NOINF MARGIN=.05) ALPHA=0.025;
    WEIGHT COUNT/zeros;
    ODS OUTPUT PdiffNoninf=noninf;
RUN;
```

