## 2. Statistical Hypotheses

Null hypothesis (H0): The success rate of cerebral angiography via TRA approach is inferior to that via TFA approach (i.e. the difference in success rates  $\leq -5\%$ );

Alternative hypothesis (H1): The success rate of cerebral angiography via TRA is not inferior to that via TFA (i.e. the difference in success rates  $> -5\%$ ).

The Wald Z test will be used for comparison between groups at one-sided significance level of 0.025. If  $p < 0.025$ , the null hypothesis H0 is rejected, supporting the conclusion that the success rate of cerebral angiography via TRA approach is not inferior to that via TFA approach.

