#### Generalized linear regression sample code:

```
PROC GENMOD DATA=adeff DESCENDING;
```

|                                                                                                                                                                                                                                                                                                                                                   |
|---------------------------------------------------------------------------------------------------------------------------------------------------------------------------------------------------------------------------------------------------------------------------------------------------------------------------------------------------|
| CLASS TRTPN AVAL;
MODEL AVAL = TRTPN / DIST=BIN LINK=LOG;
where paramcd='DCA';
ESTIMATE 'Risk Ratio for TRTPN' TRTPN 1 -1 / EXP;
ODS OUTPUT Estimates=RRCL;
RUN;                                                                                                                         |
| Results Presentation                                                                                                                                                                                                                                                                                                                       |
| 
 
• Rate estimate and 95% CI can be retained from BinomialCL.
 
• Rate difference and 95% CI can be retained from diff.
 
• P value of non-inferiority test can be retained from noninf.
 
• Risk Ratio between TRA and TFA groups and its 95% CI can be retained from RRCL.
 
 |

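### The SAP's primary-analysis sample code does not fix the event level: PROC FREQ and PROC GENMOD analyse opposite outcomes, and under the coding the code itself implies the non-inferiority test runs backwards

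*Combined protocol and SAP*

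**What the plan says.** SAP Section 2 gives the alternative hypothesis as "The success rate of cerebral angiography via TRA is not inferior to that via TFA", defined as a difference in success rates above -5 points, and adds: "The Wald Z test will be used for comparison between groups at one-sided significance level of 0.025". Section 8.1.2.2.2 repeats the method: "A Wald Z test will be used for the non-inferiority hypothesis of the primary efficacy endpoint with a non-inferiority margin of -5" (percentage points).

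Section 8.1.2.3.1 turns this into four blocks of sample code:

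- single-arm rates: "TABLE AVAL / BINOMIAL (CL=WALD) ALPHA=0.05";
- rate difference: the same table with `RISKDIFF(CL=WALD)`;
- non-inferiority test: "TABLE TRTPN*AVAL / RISKDIFF(NOINF MARGIN=.05) ALPHA=0.025";
- risk ratio: "PROC GENMOD DATA=adeff DESCENDING", with a log link, a filter on `paramcd='DCA'` and the contrast `TRTPN 1 -1`, whose output is reported as TRA versus TFA.

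The input list describes AVAL only as the response variable and TRTPN only as the planned arm. Neither coding is given. The results-presentation notes take the primary p-value from the third block. The exploratory GENMOD code in Section 10.2.3 omits `DESCENDING`.

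**The concern.** None of the three PROC FREQ blocks says which outcome level is the event, and the GENMOD block says it should be the last one. If the procedures choose opposite levels, some of the primary output describes failure under a success label. The most serious case is the third block. A non-inferiority test is directional, so applying it to failures with an unchanged margin removes its protection against a worse TRA arm. The error might also go unnoticed in the p-value, because under the planning assumptions both directions would normally pass.

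**Working it through.** **Inputs from the SAP.** Margin 5 points, one-sided level 0.025 (Section 2). "The success rates of diagnostic cerebral angiography by TRA and TFA are assumed to be 97% and 98% respectively" (Section 3). Also Section 3: "a drop-out rate of 10%, 429 cases are needed for each group to achieve a power of 90" (per cent). After 10% dropout, 429 × 0.9 = 386 evaluable per arm.

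**Assumptions not in the documents.** SAS defaults: `BINOMIAL` uses the first level; the `RISKDIFF` tests use column 1, and row 1 minus row 2; GENMOD with `DESCENDING` models the last response level. No format is attached to AVAL.

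**The plan's own figure.** The sample size does not depend on this point, but it can be reproduced. Exact enumeration of a pooled Z test with continuity correction first reaches 90% power at 386 per arm, and 386 / 0.9 = 428.9, so 429.

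**What each block delivers.**

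| Order of TRTPN | Order of AVAL | Single-arm rates | Difference and test | Risk ratio |
|---|---|---|---|---|
| TRA first | success first | success | correct | of failure |
| TRA first | 0 = failure, 1 = success | failure | reversed | correct |
| TFA first | success first | success | reversed | of failure, TFA/TRA |
| TFA first | 0 = failure, 1 = success | failure | correct (two reversals cancel) | of success, TFA/TRA |

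No row is right throughout. The code itself points to the second: `DESCENDING` yields a success risk ratio only if success is the higher value, and a `1 -1` contrast reported as TRA versus TFA implies that TRA is the first level.

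**Direction in the second row.** Let s be a success proportion, f = 1 − s, and d = s(TRA) − s(TFA). Then f(TRA) − f(TFA) = −d, and the standard error is the same for both:

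- SE = √[s(TRA)(1 − s(TRA))/n + s(TFA)(1 − s(TFA))/n]
- correct test: z = (d + 0.05)/SE, rejecting in favour of d > −0.05
- as coded: z = (−d + 0.05)/SE, rejecting in favour of d < +0.05

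**Two examples, 386 per arm.**

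- TRA 340 (88.1%), TFA 378 (97.9%): d = −0.0984, SE = 0.0180. Correct z = −0.0484/0.0180 = −2.69, p = 0.996. As coded, z = 0.1484/0.0180 = 8.24, p < 0.001. Non-inferiority is declared for an arm 9.8 points worse.
- TRA 374 (96.9%), TFA 378 (97.9%): d = −0.0104, SE = 0.0114. Correct z = 3.47; as coded, 5.28. Both pass, so the p-value would not reveal the reversal.

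**Probability of declaring non-inferiority** (exact binomial enumeration of the Wald test, TFA 98%, 386 per arm, one-sided 0.025):

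| True TRA rate | Correct direction | As coded, second row |
|---|---|---|
| 97% | 0.930 | 0.999 |
| 93% (margin) | 0.032 | 1.000 |
| 88% | 0.000 | 1.000 |

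With 429 per arm and the final-analysis boundary of 0.024 from SAP Section 4.1, the correct direction gives 0.950 at 97% and 0.032 at 93%. The reversed test gives 0.9998 at 97% and 1.0000 at 93%, 90%, 80% and 50%.

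**The case against.** Several points on the other side stand.

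- The hypothesis text is explicit and correct, and the code is headed as a sample. A final program that contradicted Section 2 would breach the SAP. A reader might infer that the trial plans to test the wrong hypothesis; the documents do not support that.
- A reader might infer that 0/1 coding alone reverses the test. It does not: TRA must also be the first TRTPN level. The SAP implies that order only through the GENMOD contrast, which sits in a different procedure from the test.
- A format on AVAL could bring the procedures into line, because GENMOD orders by formatted value by default and PROC FREQ by internal value. The FREQ blocks also read counts while GENMOD does not, so identical coding across them is assumed. The dataset specifications are not available.
- It would be too strong to say that the reversed test rejects whenever TRA fails at least as often as TFA. With 20% failure in both arms of 429, z = 0.05/√(2 × 0.16/429) = 1.83, which does not reject; the rejection probability there is about 0.45. At the rates expected in this trial the point makes no practical difference.
- `NOINF` appears to be a misspelling of `NONINF`, so the line has to be edited anyway. Whether SAS would stop on it is not established here, and it does not show what the final program contains.
- Table 4 requires success and failure counts and rates. A success rate printed at 2 to 3% would be conspicuous, so there is a good chance of detection.

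These points limit the claim without removing it. The block named as the source of the primary p-value leaves its direction to an unstated coding, and the neighbouring code suggests the harmful one.

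**Conclusion.** Wrong as written, in the sample code and not in the hypothesis. Given SAS defaults and an unformatted AVAL, no combination of codings makes all four primary blocks report success for TRA versus TFA. Under the implied coding (1 = success, TRA first) the non-inferiority block tests the reverse of the stated alternative and would pass an inferior TRA arm almost surely: about 1.00 at 93% or lower against TFA 98%, where the correct test gives about 0.03 at 93%. If TFA is the first level with 0/1 coding, the confirmatory test is right, and the harm is limited to an inverted risk ratio and single-arm failure rates. Which case applies cannot be settled from the documents. Nothing here shows that any reported result was affected.

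**What to change.** Keep the Wald method; changing the test or interval is a separate question that this defect does not raise.

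1. State in Section 8.1.2.3.1 that AVAL is 1 = success, 0 = failure, and TRTPN is 1 = TRA, 2 = TFA.
2. Use `BINOMIAL(LEVEL='1' CL=WALD)` for the rates, `RISKDIFF(CL=WALD COLUMN=2)` for the difference, and `RISKDIFF(NONINF MARGIN=0.05 METHOD=WALD COLUMN=2)` for the test, which also corrects the keyword.
3. Name the event level explicitly in both GENMOD blocks, including the exploratory one in Section 10.2.3.
4. Filter every block on `paramcd='DCA'`; at present only the primary GENMOD block does so.
5. Before database release, run the program on dummy data with TRA clearly inferior (for example 340 versus 378 successes of 386) and confirm that it does not declare non-inferiority.

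The cost is two coding definitions, a few options and one dummy-data run. Design, sample size and data collection are unchanged.
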